### Data collection and management

2.9

Outcome and safety variables will be systematically collected across three distinct phases: preoperative, intraoperative, and postoperative. During the preoperative phase, demographic data, medical history, surgical information, laboratory values, and baseline assessments, including AIS, HADS, NRS for pain, and QoR-15, will be recorded at the enrolment visit immediately preceding the initial taVNS session. In the intraoperative phase, data on the duration of anesthesia and surgery, tracheal intubation time, estimated blood loss, fluid infusion volume, medication administration, and continuous EEG parameters will be meticulously documented. Postoperatively, the AIS and HADS will be assessed in the evenings of POD 1, 2, and 3. Additionally, the QoR-15 and NRS pain scores, both at rest and during movement, will be evaluated on the morning of POD 1, alongside the documentation of clinical outcomes and any adverse events.

All data will be systematically recorded using standardized case report forms (CRFs) and subsequently double-entered into an encrypted electronic database by two independent research assistants. A random sample comprising 10% of the CRFs, stratified according to the enrolment sequence, will undergo verification against the original medical records. The data manager will be responsible for generating queries related to missing or inconsistent values, with the principal investigator overseeing their resolution. In compliance with institutional policy and ICH-GCP guidelines, original CRFs will be securely stored in a locked cabinet with restricted access for a minimum duration of 5 years. The electronic data will be hosted on hospital servers, safeguarded by SSL encryption, automated backups, and role-based access control, ensuring access is limited to authorized study personnel.

### Sample size calculation

2.10

The primary outcome is the incidence of POSD on POD 1, defined as an AIS score ≥ 6. Based on our internal pilot study (*N* = 20; taVNS *n* = 10, sham *n* = 10), the incidence of POSD (AIS ≥ 6) was 20% in the taVNS group compared to 45% in the sham group. Sample size was calculated using PASS 15.0 (NCSS, LLC) for a two-sided chi-square test comparing two independent proportions, with the following parameters: P1 (sham) = 0.45, P2 (taVNS) = 0.20, α = 0.05 (two-sided), power = 0.80. This calculation indicated a need for 52 evaluable participants per group. Accounting for an anticipated 10% dropout rate based on comparable perioperative neuromodulation trials, the final target enrollment is 116 participants (58 per group).

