From a methodological perspective, the intervention protocol employed in this study is designed to adhere to standard taVNS parameters. The stimulation will be administered to the left cymba conchae, a region abundant in auricular vagal branches, at a frequency of 20 Hz with a pulse width of 250 μs. These parameters were selected based on previous efficacy studies related to chronic insomnia and cortical oscillation research, aiming to optimize the balance between tolerability and effective activation of the vagus nerve-thalamus-cortex pathway (32, 38). The sample size calculation is informed by internal pilot data, indicated a reduction in the incidence of POSD, defined as AIS score of 6 or higher, from 45% in the sham group to 20% in the taVNS group–an absolute risk reduction of 25 percentage points. To achieve 80% statistical power for detecting this difference in proportions at a two-sided significance level of α = 0.05, while accounting for a 10% dropout rate, a sample size of 58 participants per group will be required.

This study is subject to several limitations. To begin with, the single center design might restrict how widely the findings can be applied, since local patient traits like age distribution, initial sleep condition, and the complexity of surgeries could influence the intervention’s effectiveness. Nevertheless, the single-center setting enables standardization of surgeons, anesthesia protocols, and postoperative ward environments, thereby reducing confounding from institutional practice variations that frequently obscure treatment effects in multicenter perioperative trials. Secondly, our sample size estimation relies on internal pilot data. With a total of 116 participants, the study lacks sufficient power for conducting subgroup analyses, detecting rare adverse events, or making stratified comparisons based on age, operative duration, or anesthetic dosage. Thirdly, the primary observation window of 3 days may not capture longer-term effects on chronic sleep disturbances, delayed cognitive function, or sustained autonomic regulation.

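### The 45% sham rate behind the sample size cannot come from a pilot arm of 10 patients, so the stated 80% power rests on an input with no possible source

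*Protocol article*

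**What the plan says.** Section 2.10 of the protocol article describes an internal pilot of 20 patients, with arms given as "taVNS *n* = 10, sham *n* = 10". It reports as a result of that pilot that "the incidence of POSD (AIS ≥ 6) was 20% in the taVNS group compared to 45% in the sham group". The two percentages then become the design inputs, "P1 (sham) = 0.45, P2 (taVNS) = 0.20, α = 0.05 (two-sided), power = 0.80", for a "two-sided chi-square test comparing two independent proportions". The stated outcome is: "This calculation indicated a need for 52 evaluable participants per group". A 10% allowance for dropout brings this to 58 per group, 116 in total.

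The Discussion repeats the same drop, "from 45% in the sham group to 20% in the taVNS group", as a finding of the internal pilot, describes it as a 25-point absolute reduction, and lists reliance on pilot data as a limitation. The article gives no other source for the 45%. The Abstract and Introduction cite a POSD incidence of up to 62% in this population, but the calculation does not use that figure.

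**The concern.** POSD is defined as AIS ≥ 6, so each pilot patient either has it or does not. In an arm of 10 the incidence must be a whole number of tenths. The taVNS figure of 20% is 2/10 and is possible. The sham figure of 45% is not. Therefore the arm size, the percentage, or the claim that the rate was observed is wrong.

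This matters because the sham rate is one of the two rates that fix the trial's size. It sets the 52 evaluable per group, the 116 enrolled and the 25-point effect quoted in the Discussion. If the pilot count was really 4/10, the trial has been planned at well under 80% power for the effect the pilot showed. If it was 5/10, it has been planned at well over 80%. A reader who later weighs a null primary result against the stated 80% power has no sound basis for doing so.

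**Working it through.** **Inputs (section 2.10).** Pilot arms 10 and 10; reported incidence 45% sham and 20% taVNS; two-sided α = 0.05; power 0.80; chi-square test; 52 evaluable per group; 10% dropout; 58 enrolled per group. Allocation is 1:1 (section 2.3).

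**1. Reproducing the plan's figure from its own inputs.** With p1 = 0.45 and p2 = 0.20, the difference is d = 0.25 and the mean rate is 0.325.

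- Pooled formula: n = [1.960 × √(2 × 0.325 × 0.675) + 0.842 × √(0.45 × 0.55 + 0.20 × 0.80)]² / 0.25² = (1.298 + 0.537)² / 0.0625 = 53.9, so 54 per group.
- Unpooled formula: n = (0.2475 + 0.16) × (1.960 + 0.842)² / 0.0625 = 51.2, so 52 per group.
- Power at 52 per group: 78.5% by the pooled formula, 79.3% by exact enumeration of the Pearson test.
- Dropout: 52 / 0.90 = 57.8, so 58 per group and 116 in total.

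The stated sample size therefore follows from the stated rates.

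**2. Can the pilot have produced the rates?**

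- taVNS: 0.20 × 10 = 2 patients. Possible.
- sham: 0.45 × 10 = 4.5 patients. Not possible. The neighbouring values are 4/10 = 40% and 5/10 = 50%.
- One sham patient missing: 4/9 = 44.4%, which rounds to 44%, and 5/9 = 55.6%.
- Of all denominators up to 20, only 5/11 (45.5%) and 9/20 (45.0%) lie within half a point of 45%. Neither fits a sham arm of 10.

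**3. What the nearest possible counts do to the design.** taVNS is held at 20%, with a two-sided chi-square test at α = 0.05 and the pooled formula: power = Φ{[d√n − 1.960 × √(2p̄(1 − p̄))] / √(p1(1 − p1) + p2(1 − p2))}.

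For example, sham 40% at n = 52: (0.20 × 7.211 − 1.960 × √0.42) / √0.40 = (1.442 − 1.270) / 0.632 = 0.272, and Φ(0.272) = 60.7%.

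| Sham rate | Power at 52 per group (exact) | Power at 58 per group | n per group for 80% power | With 10% dropout |
|---|---|---|---|---|
| 40% (4/10) | 60.7% (61.8%) | 65.5% | 82 | 92 (184 total) |
| 45% (as stated) | 78.5% (79.3%) | 82.9% | 54 | 60 (120 total) |
| 50% (5/10) | 90.6% (91.0%) | 93.4% | 39 | 44 (88 total) |

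**4. How much a pilot of this size can say.** Taking the stated rates at face value, the standard error of the difference is √(0.45 × 0.55/10 + 0.20 × 0.80/10) = 0.202. The 95% interval is 0.25 ± 1.96 × 0.202, or about −15 to +65 points. Exact 95% intervals for the possible counts are 12% to 74% for 4/10, 19% to 81% for 5/10 and 3% to 56% for 2/10.

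**The case against.** The best case for the plan is that power depends on the true event rates, not on the pilot count. A true sham rate of 45% is compatible with 4/10 and with 5/10, and nothing in the article makes 45% implausible as a planning value. The calculation is conditional on its inputs and reproduces from them. The primary analysis in section 2.11, a chi-square test with an absolute risk reduction and its confidence interval, uses neither the pilot rate nor the planned power, so type I error and the estimate are untouched. The Discussion already admits reliance on pilot data.

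Most of this stands, and it limits how the consequence should be read. The 61% and 91% are planning powers if the true sham rate were exactly 40% or 50%. They show how sensitive the design is to the disputed input and do not measure the trial's actual power. The pilot's wide interval is a supporting remark only; the contradiction does not depend on it.

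None of this removes the contradiction. The article does not offer 45% as an assumption. It reports it as an observed incidence in an arm whose size it also prints, and the two cannot both be right. Admitting that the sample size relies on a pilot does not repair a pilot figure that cannot have occurred.

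**Conclusion.** The concern holds. As written, the sham rate that sets the sample size cannot have been observed in the pilot cited as its only source. The arithmetic from 45% and 20% to 52 and 58 per group is sound; the input is not. Replacing 45% by the nearest possible pilot values moves planning power at 52 per group from about 79% to about 61% or 91%, and the required evaluable number to 82 or 39 per group. The article does not show which direction applies.

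These figures assume that taVNS stays at 20%, that the test is a two-sided chi-square test at 0.05, and that the true count is one of the two nearest to 4.5 out of 10. If the pilot arm was not in fact 10 patients, other values are possible. The validity of the primary test and estimate is not in question. The point must be corrected because the trial's size and stated power rest on this figure.

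**What to change.** - Return to the pilot data and report counts with denominators for each arm. Correct section 2.10 and the matching statement in the Discussion.
- Restate the power that 52 evaluable and 58 enrolled per group give at the corrected rates.
- If 45% was a planning assumption, say so, justify it, and show power at 52 per group for sham rates of 40%, 45% and 50% (about 61%, 79% and 91%).
- As a clarification, confirm that the 20 pilot patients are not counted among the 116. The article does not suggest that they are.

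The cost is a text correction, with no extra patients and no change to endpoint or analysis. The restated power may be less favourable. If the sham count proves to be 4/10, the sponsor should know this before the trial reads out and state openly the power at which 116 is being kept.

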### Statistical analysis

2.11

Statistical analyses will be performed using SPSS Statistics 26.0 (IBM Corp.) and R 4.4.0 (R Foundation). MATLAB R2018b (MathWorks, Natick, MA) will be employed for the preprocessing and spectral analysis of EEG data. Normality will be assessed using the Shapiro-Wilk test and Q-Q plots. Continuous variables will be presented as mean ± standard deviation or median (interquartile range), and categorical variables will be shown as frequencies and percentages.

The primary outcome (incidence of AIS ≥ 6 on POD 1) will be analyzed using the chi-square test to compare proportions between the taVNS and sham groups. The effect size will be expressed as an absolute risk reduction with a 95% confidence interval. Linear mixed-effects models will analyze repeated measures, including (1) AIS total scores (Pre 1 to POD 3); (2) HADS-A and HADS-D (as two separate scales, Pre 1 to POD 3); (3) objective sleep parameters from actigraphy; and (4) EEG spectral power across five bands (delta, theta, alpha, beta, and gamma) at six time points (T0–T5). Models include fixed effects for group, time, group × time interaction, and random intercepts for subjects. For repeated clinical outcomes, Bonferroni correction will be applied across four key endpoints: HADS-A, HADS-D, AIS trajectory, and objective sleep parameters from actigraphy, yielding a significance threshold of α = 0.0125 (0.05/4). For EEG spectral analyses, given the exploratory nature and high dimensionality (5 frequency bands × 6 timepoints), the Benjamini–Hochberg procedure will control the false discovery rate at q < 0.05.

A three-step approach will be used to identify predictors of POSD: (1) Univariate screening (*P* < 0.10) for 30 EEG variables (5 bands × 6 timepoints); (2) LASSO regularization (10-fold CV) to select independent predictors; (3) Multivariable logistic regression reporting ORs and 95% CIs.

The main analysis will adhere to the intention-to-treat methodology. To address missing data, multiple imputation via chained equations will be utilized, generating 20 imputations under the assumption that data are missing at random. Sensitivity analyses will incorporate pattern-mixture models to account for mechanisms where data are missing not at random. The per-protocol analysis will exclude cases with significant protocol deviations. Effect sizes will be reported as Cohen’s d, alongside 95% confidence intervals.

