#### Inclusion criteria

2.2.1

Participants will be eligible if they are aged 18–65 years, classified as ASA physical status I–II, have a BMI between 18 and 30 kg/m^2^, and be scheduled for elective gynecologic laparoscopic surgery expected to last at least 60 min. Additionally, they must be proficient in Mandarin Chinese with the ability to provide written informed consent.

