#### Criteria for exclusion

2.2.2

(1) Broken skin, infection, or inflammation of the external ear or auditory canal; history of tinnitus, Meniere’s disease, or cardiac arrhythmia with symptoms; (2) Presence of an implanted cardiac pacemaker, defibrillator, or other active implantable device; (3) History of neuropsychiatric disorders, such as depression, anxiety, epilepsy, or schizophrenia; (4) Severe hepatic impairment (Child-Pugh class B or C) or renal impairment (eGFR < 60 mL/min/1.73 m^2^ as per the CKD-EPI equation); (5) Planned postoperative ICU admission; (6) Pregnancy or breastfeeding.

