#### Main outcome

2.7.1

The primary endpoint is the incidence of POSD on POD 1, defined as an Athens Insomnia Scale (AIS) score ≥ 6. The AIS is a validated eight-item instrument measuring nocturnal sleep parameters and daytime functioning, with total scores ranging from 0 to 24 (22).

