#### Secondary outcomes

2.7.2

Trajectory of Postoperative Sleep Quality (1) Subjective sleep quality: The trajectory of AIS total scores from Preoperative Day 1 (Pre-1) through POD 3. (2) Objective sleep parameters: Wrist actigraphy (HUAWEI WATCH GT2) measured continuously from Pre-1 through POD 3. Metrics include sleep continuity (latency, awakenings, wake after sleep onset, efficiency, and total sleep time) and sleep architecture (duration of light, deep, and REM sleep).Anxiety and Depression The Hospital Anxiety and Depression Scale (HADS) will evaluate anxiety (HADS-A) and depression (HADS-D) at Pre-1, POD 1, POD 2, and POD 3. Each subscale comprises seven items scored 0–3; scores ≥ 8 indicate probable anxiety or depression (23).Postoperative Pain and Recovery Quality Pain intensity will be assessed using the Numeric Rating Scale (NRS, 0–10) at rest and during movement on POD 1 (24). Analgesic consumption and patient-controlled analgesia demands will be recorded. Recovery quality will be evaluated on POD 1 using the 15-item Quality of Recovery (QoR-15) questionnaire (scores 0–150, higher scores indicating better recovery) (25).Quantitative EEG Parameters (1) Absolute power: The integral of the power spectral density (PSD) over respective frequency bands (delta 1–4 Hz, theta 4–8 Hz, alpha 8–12 Hz, beta 12–25 Hz, and gamma 25–45 Hz). (2) Peak frequency: The frequency at which maximum PSD occurs within each band.

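### The primary chi-square test is valid but leaves baseline AIS, already collected, out of the analysis and so gives up some precision

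*Protocol article*

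**What the plan says.** Main outcome (2.7.1): "The primary endpoint is the incidence of POSD on POD 1, defined as an Athens Insomnia Scale (AIS) score ≥ 6". The definition makes no reference to the preoperative score.

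Statistical analysis (2.11): this outcome "will be analyzed using the chi-square test to compare proportions between the taVNS and sham groups". The same section adds: "The effect size will be expressed as an absolute risk reduction with a 95% confidence interval". No covariate is named for either.

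Baseline AIS is available. Data collection and management (2.9) states that "baseline assessments, including AIS, HADS, NRS for pain, and QoR-15, will be recorded at the enrolment visit", before the first session, and Table 1 schedules both AIS and PSQI at Pre1. The only stated analytic use of the baseline AIS value is as a time point in the mixed model for a secondary outcome, "The trajectory of AIS total scores from Preoperative Day 1 (Pre-1) through POD 3".

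Nothing in the design controls baseline sleep:
- The inclusion criteria (2.2.1) require patients to be "aged 18–65 years, classified as ASA physical status I–II, have a BMI between 18 and 30", plus type and length of surgery, language and consent.
- The nearest exclusion (2.2.2) is "History of neuropsychiatric disorders, such as depression, anxiety, epilepsy, or schizophrenia". Insomnia, AIS, PSQI and hypnotic use are not named.
- Randomisation (2.3) uses permuted blocks of 4 and 6, with no stratification described.

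**The concern.** The outcome is a score cut at 6, and the same score is measured in the same patients shortly before treatment. If the earlier score predicts the later one, leaving it out of the primary analysis leaves explainable variation in the treatment comparison. The trial is sized for 80% power with little margin, so a few points of power at no extra recruitment are worth having.

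There is a second, separate matter. Because entry is not limited by baseline sleep, a woman with AIS ≥ 6 before surgery who still scores 6 or more on day 1 counts in the *incidence*, although nothing new has happened to her. The article presents the intervention as preventive, so readers will want to know how much of the result concerns new cases.

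**Working it through.** **1. The plan's own figure.** Inputs from Sample size calculation (2.10): 0.45 v 0.20, two-sided α = 0.05, power 0.80.

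n per arm = (1.960 + 0.842)² × [0.45×0.55 + 0.20×0.80] / 0.25² = 7.849 × 0.4075 / 0.0625 = 51.17, so 52. Then 52 / 0.90 = 57.8, so 58 per arm and 116 in total. The stated numbers reproduce (the pooled-variance formula gives 54). The sample size is not in question here.

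**2. Precision of the unadjusted comparison.** SE of the risk difference with 52 per arm = √(0.4075 / 52) = 0.0885. Power = Φ(0.25/0.0885 − 1.960) = Φ(0.864) = 0.806.

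**3. Effect of adjusting for baseline AIS.** The correlation r between baseline and day 1 AIS is an assumption. The simulation used 4,000 trials per setting and 52 per arm. Baseline was standard normal, and latent day 1 AIS = r × baseline + √(1 − r²) × noise, cut so that the arm rates are 0.45 and 0.20. The chi-square test was compared with a logistic model on arm and baseline, standardised to the risk difference.

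| Assumed r | Power, chi-square | Power, adjusted | Variance ratio, adjusted/unadjusted |
|---|---|---|---|
| 0 | 0.80 | 0.80 | 1.01 |
| 0.3 | 0.79 | 0.82 | 0.95 |
| 0.5 | 0.81 | 0.87 | 0.87 |

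A second, separate simulation gave 0.80 v 0.80, 0.79 v 0.82 and 0.80 v 0.86, with the same variance ratios. Differences of 0.01 are close to simulation error: √(0.8×0.2/4000) = 0.006.

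**4. Cross-check by formula.** Dividing 0.25/0.0885 = 2.824 by the square root of the variance ratio:
- ratio 0.95: 2.824/0.975 = 2.897, power Φ(0.937) = 0.83
- ratio 0.87: 2.824/0.933 = 3.028, power Φ(1.068) = 0.86

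Both agree with the simulations.

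**5. Validity.** With equal rates of 0.45 in both arms and r = 0.5, the rejection rate was 0.060 for the chi-square and 0.059 for the adjusted risk difference. Adjustment carries no meaningful type I error cost. In the runs behind the table, the mean estimated risk difference stayed near 0.25 with either method, so the quantity estimated is the same.

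**The case against.** The strongest reply is that nothing here is wrong. An unadjusted chi-square with an absolute risk reduction is valid in a randomised trial and matches the test used for the sample size. It is also simple to explain. The gain from adjustment depends on a correlation that the documents do not give. The Introduction attributes the condition largely to anaesthetics, surgical inflammation and sympathetic activation, so a strong link with the preoperative score cannot be taken for granted. At r = 0.3 the gain is only 2 to 3 power points, and at r = 0 there is none. Baseline AIS does enter the secondary AIS model, and supportive adjusted analyses are often left to a statistical analysis plan, which is not shown.

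Most of this stands, and it limits the point to efficiency. It does not dispose of it. The article fixes the primary test outright, so this concerns a stated choice rather than a detail left for later. The covariate is already collected, the downside at r = 0 is a variance ratio of 1.01, and the secondary model does nothing for the primary comparison.

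A reader might also infer that the chi-square cannot be combined with the planned 20 imputations. The documents do not support that. The plan already states an absolute risk reduction, which pools directly, and chi-square statistics can themselves be combined across imputed datasets.

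**Conclusion.** The point holds as a worthwhile improvement to a valid primary analysis. With 52 per arm and 45% v 20%, adjustment leaves power at about 80% if r = 0, and raises it to about 82% at r = 0.3 and about 86% at r = 0.5. The variance of the risk difference falls by about 0%, 5% and 13%. These figures rest on the assumed r, a normal latent score and a continuous baseline.

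Three stronger readings are not supported:
- **Bias from chance imbalance.** Imbalance in pre-existing insomnia does not pass straight into the risk difference. It does so only in proportion to its association with the day 1 outcome, and the unadjusted confidence interval already allows for it.
- **Adjustment cures the counting of existing cases.** It does not. The outcome stays AIS ≥ 6 on day 1, so those patients still count; this needs its own supporting analysis.
- **The trial is underpowered because of existing cases.** The pilot rates of 45% and 20% are given for the same AIS ≥ 6 definition and may already include such patients. The pilot's entry criteria are not stated, so no shortfall is shown.

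**What to change.** Before unblinding, amend Statistical analysis (2.11) as follows:

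1. Make the primary analysis a logistic regression of day 1 AIS ≥ 6 on arm and baseline AIS total score. Standardise it over the trial population to the absolute risk reduction already stated, with a 95% confidence interval (delta method or bootstrap), and pool it over the imputations. The standardisation matters because the model's odds ratio would be a different effect measure.
2. Keep the chi-square test and the unadjusted risk difference as support.
3. Separately, report new-onset sleep disturbance by arm among participants with baseline AIS < 6, labelled descriptive.

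The cost is wording and analysis code. The data are already scheduled, and the effect measure and sample size of 116 do not change. The change has to be made before allocation is known, since a covariate added afterwards would look chosen for its result.

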
### EEG power spectrum processing

2.5

Frontal quantitative EEG parameters will be obtained using the ConView YY-105 anesthesia depth monitoring system, employing bilateral frontal electrodes at a sampling rate of 500 Hz. EEG power spectral density will be estimated using the multitaper method (15 tapers, time-half bandwidth product = 8) with a 4-s window length and 50% overlap (2-s step), implemented in MATLAB’s pmtm function. The bandpass filter (0.5–45 Hz) will be applied as a zero-phase filter using forward-reverse filtering to avoid phase distortion. Artifact-free epochs will be extracted at six predetermined time points: T0 (pre-stimulation baseline): 5 min prior to the first taVNS session; T1 (preoperative sustained stimulation), 20–30 min following the initiation of taVNS; T2 (post-induction), 5 min after tracheal intubation; T3 (intraoperative maintenance), 20 min subsequent to the skin incision; T4 (peri-extubation), at the conclusion of surgery, immediately preceding emergence from anesthesia; and T5 (postoperative sustained stimulation), 20–30 min after the initiation of postoperative taVNS.

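### EEG band power enters an additive random-intercept model with no log scale named and awake and anaesthetised epochs pooled; in bands that rise under anaesthesia, an awake taVNS effect would be largely missed

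*Protocol article*

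**What the plan says.** Section 2.7.2 lists quantitative EEG among the secondary outcomes and defines "Absolute power: The integral of the power spectral density (PSD) over respective frequency bands", with five bands from delta to gamma. Section 2.11 puts "EEG spectral power across five bands (delta, theta, alpha, beta, and gamma) at six time points (T0–T5" into linear mixed-effects models and gives their form: "Models include fixed effects for group, time, group × time interaction, and random intercepts for subjects". No transformation, relative power or baseline ratio is mentioned, and no residual structure beyond the random intercept.

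Section 2.11 also says "Normality will be assessed using the Shapiro-Wilk test and Q-Q plots". The sentence after it covers how variables are summarised. No consequence for the models is stated.

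Section 2.5 fixes the six epochs. T0 and T1 precede induction, and T5 falls during the session that starts after extubation. T2 follows intubation, T3 follows incision, and T4 is taken "at the conclusion of surgery, immediately preceding emergence from anesthesia". One model therefore spans three epochs outside anaesthesia and three under it.

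Section 2.11 calls the EEG analyses exploratory and states that "the Benjamini–Hochberg procedure will control the false discovery rate at q < 0.05". A separate predictor analysis for POSD starts with univariate screening "for 30 EEG variables (5 bands × 6 timepoints".

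**The concern.** An integral of the power spectral density cannot be negative. If patients and anaesthetic states differ mainly by a factor, an additive subject intercept does not remove the patient effect on the raw scale, and epochs with higher power also have higher variance. A random-intercept model with one residual variance averages that variance over all six epochs and uses the average for every contrast, including T1 versus T0.

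That contrast is the cleanest view of stimulation: the patient is awake, the device is on, and the patient's own baseline comes just before. If the anaesthetised epochs inflate its standard error, a real proportional change would be reported as absent. The Discussion says the mechanistic EEG data would be informative even if the trial is null, so an EEG null produced by the analysis scale would mislead that use.

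**Working it through.** **The plan's own figure.** There is no power statement for EEG. The only sample-size figure is for the primary outcome: (1.96 + 0.8416)² × (0.45 × 0.55 + 0.20 × 0.80) / 0.25² = 7.849 × 0.4075 / 0.0625 = 51.2, so 52 per group, and 52 / 0.9 = 57.8, so 58. Both agree with section 2.10. I use n = 52 per arm.

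**Assumed inputs (not in the documents).** Log-normal power; central log-SDs 0.6 between patients (s_b) and 0.3 within (s_w); a 20% rise at T1 and T5 under active taVNS; power at T2–T4 equal to r times awake power; nominal two-sided 0.05 before Benjamini–Hochberg.

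**Log scale.** SE of the between-arm difference in T1−T0 = √(4 s_w²/n) = √(4 × 0.09/52) = 0.0832. Effect = ln 1.2 = 0.1823. Ratio = 2.19, so power = Φ(2.19 − 1.96) = 59%, whatever r is.

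**Raw scale** (awake median set to 1).
- K = exp(0.36 + 0.09) = 1.568. Awake variance V = K(K − 1) = 0.891. Awake covariance C = K(exp(0.36) − 1) = 0.680.
- Effect = 0.2 × exp(0.225) = 0.2505. True SE of the contrast = √(4(V − C)/52) = 0.1276.
- Let A = V(3 + 3r²). The model's residual mean square is MS = [A − {A + C((3 + 3r)² − 3 − 3r²)}/6] / 5, and its SE is √(4 MS/52).
- Power ≈ P(Z > (1.96 × model SE − 0.2505)/0.1276).

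| r | MS | Model SE | Approximate raw power |
|---|---|---|---|
| 1 | 0.212 | 0.128 | 50% |
| 2 | 0.733 | 0.238 | 5% |
| 3 | 1.874 | 0.380 | below 0.1% |

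At r = 2 the model's SE is 0.2375/0.1276 = 1.86 times the true one; at r = 3 it is 2.98 times.

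**Simulation of the planned model, same assumptions, T1 versus T0.**

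| r | Raw | Log |
|---|---|---|
| 0.3 | 46% | 60% |
| 0.6 | 52% | 58% |
| 1 | 48% | 60% |
| 1.5 | 26% | 59% |
| 2 | 6% | 59% |
| 3 | 0.2% | 59% |

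At r of 2 or more, the raw test rejects a true null close to 0% of the time, so it is miscalibrated as well as weak.

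**Scale separated from pooling.** With T0 and T1 only, the anaesthetised epochs drop out. Raw versus log power is then 55% vs 59% (SDs 0.4/0.3), 46% vs 59% (0.6/0.3) and 25% vs 38% (0.8/0.4). Over all runs the cost of scale alone is about 3 to 16 points. The collapse at r of 2 or more comes from the common residual variance.

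**Other assumptions.** With a 30% rise and SDs 0.6/0.45, raw versus log power for T1 is 46% vs 56% at r = 1, 10% vs 54% at r = 2 and 0.5% vs 55% at r = 3. The group × time test falls from about 75% on the log scale to 24% (r = 2) and 12% (r = 3) on the raw scale. At r of 0.3 to 0.6 the raw T1 contrast keeps 52–54% against 55–57%, but its null rejection is 9–10%. With 58 per arm the pattern is the same.

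**The case against.** The strongest reply is that nothing in the article says raw or untransformed. Section 2.7.2 defines a quantity, and its dB value could still be called absolute power. A normality check is planned and is not expressly limited to summaries. A transformation rule could sit in an analysis plan that is not shown. This stands as a limit: the raw scale is inferred from the definition and from silence. It does not dispose of the point. The article states the outcome, the model terms and the false discovery rule, and those terms followed as written give the weaker analysis.

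A reader might infer more than the documents support:
- **That anaesthesia swamps the EEG result in general.** The documents give no anaesthetised-to-awake ratio for any band, and no collapse occurs where power is flat or falls. With SDs 0.4/0.3 and r of 0.3 to 0.6, raw power is even slightly higher (61–62% vs 58%), though such raw contrasts tend to be liberal.
- **That a few high-power patients swamp the effect.** Skew between patients costs far less than the pooled variance does.
- **That the predictor model is driven by its largest values.** No calculation supports this; using log values there is a matter of consistency.
- **That the log scale secures the finding.** It still misses the assumed effect about 41% of the time in the central case. The simulations also assume log-normal data and a proportional effect, which favours the log model by construction.

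**Conclusion.** The point holds in a limited form. As written, sections 2.7.2 and 2.11 pair a positive, probably multiplicative outcome with an additive random-intercept model that pools awake and anaesthetised epochs. Under the stated assumptions the scale alone costs roughly 3 to 16 points of power for T1 versus T0. In bands that at least double under anaesthesia, raw-scale power is about 13% or less, and near 0% at a threefold rise, against 36–60% on the log scale. Which bands are affected cannot be told from the documents. The matter is confined to the exploratory EEG analysis among the secondary outcomes; the primary endpoint and the sample size are untouched.

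**What to change.** In sections 2.7.2 and 2.11, state that log-transformed absolute power (10·log10, dB) is the outcome in the mixed models, and that group effects are reported as ratios of geometric means with 95% confidence intervals. Let the residual variance differ by time point, since pooling is what causes the largest loss. Use the same log values in the POSD predictor analysis for consistency.

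The cost is a sentence or two of analysis wording, with no added data or patients. The downside is that effects are read as ratios and not in raw power units.
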